**Methods/design:**

This is a single-centred randomized controlled intervention trial (prospective) comparing standard-of-care with standard-of-care plus a mobile phone-based SMS intervention for 6 months. A total of 216 participants with newly diagnosed type 2 diabetes will be recruited. Data will be collected at the outpatient department of Bangladesh Institute of Health Science (BIHS) hospital at baseline and after 6 months. The primary outcome measure will be change in HbA1c between baseline and 6 months. The secondary outcome measures are self-reported medication adherence, clinic attendance, self-reported adoption of healthy behaviours, diabetes knowledge, quality of life and cost effectiveness of the SMS intervention. The inclusion criteria will be as follows: diagnosed as patients with type 2 diabetes by the BIHS physician, using oral medication therapy, living in Dhaka city, registered with the BIHS hospital, using a mobile phone, willing to return for follow up after 6 months and providing written informed consent. Participants will be allocated to control and intervention arms after recruitment using a randomization software. Data will be collected on socio-demographic and economic information, mobile phone use and habits, knowledge of prevention, management and complications of diabetes, self-perceived quality of life assessment, self-reported diseases, medical history, family history of diseases, medication history, medication adherence, health seeking behaviour, tobacco use, physical activity, diet, mental health status, life events and disability, anthropometric measurements of weight, height, blood pressure and blood tests for HbA1c.

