### Sample size

Assuming that standard care with metformin reduces HbA1c by 1% on average and the intervention adds another 0,5% [15,16]. Assuming a SD of 1, which seems reasonable and an alpha error level of 5%, the two-tailed calculation gives a power of over 90% with only 90 participants in each arm of the study. Considering 20% loss of follow up by 6 months total sample size required for this study will be 216.

**Inclusion criteria:**Diagnosed as type 2 diabetic patient according to WHO criteriaCurrently on oral Metformin monotherapy and able to afford cost for 6 months treatmentPatients with a personal mobile phonePatients who know how to retrieve/read SMS on mobile phone (Bangla with English alphabets)Willingness to receive SMS for 6 months at least one SMS per day.Patient registered with the BIHS health centre and lives in Dhaka City.Provide written informed consent and agree for a follow up visit after 6 months. (SMS reminders will be sent for the follow up visit).

**Exclusion criteria:**Patients with other types of diabetes, such as diagnosed as type 1 diabetes, gestational diabetes.Patients whose clinical condition might have interfered with the study such as mental illness, other serious illness or co-morbidities requiring hospitalization.Patients unable to give their informed consent or agree for follow up visit.Patients who do not own a mobile phone or cannot read SMS messages.Patients who reside outside Dhaka city.

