### Data collection and intervention

Data will be collected at baseline (0 month) and after 6 months through questionnaires, physical measurements and blood tests (Figure 1). We will send out mobile phone SMS to patients in the intervention group for medication reminders and health education about diabetes, its complications, diet and physical activity. SMS content has been developed using different national and international guidelines for diabetes and will be field tested for clarity and contents. The patients will be encouraged to send messages/call the study team for any queries encountered in response to the text messages. The study team will then call patients who had a problem within 2 working days. Study staff will maintain a study register to record all SMS responses and other mobile phone communications with patients in a study log.

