### Primary outcome measures

[Time Frame: 6 months]Disease progression (HbA1c level).

The primary analysis will be intention to treat which will provide relative unbiased comparisons among the intervention and control groups. It will also reduce the effects of crossover and dropout, which may break the random assignment to the treatment groups in a study.

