### Data analysis

Data coding, quality control and data entry will be done following established procedures at the International Center for Diarrhoeal Diseases Research, Bangladesh (icddr, b). Precoded questionnaire will be used to minimize data coding errors. All data forms and questionnaires will be checked for errors and necessary corrections will be made before data entry. A data entry programme with built-in range and consistency checks will be used. Frequency distributions will be run to identify outliers. In all analyses, potential confounding variables and effect modifiers will be considered.

Basic presentations of data will include number and percentages of cases with diabetes by age, sex, location of residence, and in relation to different known risk factors. Chi-square tests will be used to assess the association between diabetes and risk factors. Prevalence odd ratios will be calculated for diabetes adjusted for major confounding variables (e.g. age, sex, smoking habits, socioeconomic status, nutritional status, family history of diabetes). Interaction between age and risk factors, obesity and diabetes risk factors, and nutritional status and risk factor (hypertension and diabetes risk factors) will also be examined in the logistic regression model.

Effect of intensive mobile phone SMS intervention will be examined by comparing the longitudinal change in glycated hemoglobin (HbA1c) level changes between intervention and control groups. The change in HbA1C will be defined as the difference between mean HbA1c at the first survey and minus that at the second survey and standardized for the time between surveys. We will analyze the primary outcomes with the t-test. The primary analysis will be intention to treat which will provide relative unbiased comparisons among the intervention and control groups. It will also reduce the effects of crossover and dropout, which may break the random assignment to the treatment groups in a study. Relative risk (RR) will be reported for non-adherence, with an RR less than 1 suggesting better outcome for the intervention group. As a measure of absolute effect size, we will also calculate the number needed to treat (NNT) and its associated 95% CI for both unadjusted primary outcomes. Adjusted analyses by fitting a logistic regression model to the primary outcomes with adjustments for sex, age, baseline HbA1c level will be performed.

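### The primary HbA1c comparison is an unadjusted change-score t-test, and the only baseline-adjusted model planned is a logistic regression that does not suit a continuous outcome

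*Protocol article*

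**What the plan says.** The Abstract names a single continuous primary outcome: "The primary outcome measure will be change in HbA1c between baseline and 6 months". The Data analysis section defines the change as the "difference between mean HbA1c at the first survey and minus that at the second survey and standardized for the time between surveys", and then states: "We will analyze the primary outcomes with the t-test".

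The same section plans a number needed to treat with "its associated 95% CI for both unadjusted primary outcomes". It follows this with the only adjusted model for the primary outcome: "Adjusted analyses by fitting a logistic regression model to the primary outcomes with adjustments for sex, age, baseline HbA1c level will be performed".

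On the analysis population, both Primary outcome measures and Data analysis name intention to treat and say of it: "It will also reduce the effects of crossover and dropout, which may break the random assignment to the treatment groups in a study". The Sample size section plans for attrition: "Considering 20% loss of follow up by 6 months". There are only two measurement times: "Data will be collected at baseline (0 month) and after 6 months through questionnaires, physical measurements and blood tests". The Discussion places the baseline blood sample before randomisation.

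**The concern.** There are two linked issues.

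The first is the choice of test. Baseline HbA1c is measured before randomisation, and the investigators think it worth adjusting for, yet the primary test does not use it as a covariate. The model that does use it is logistic. A logistic model needs a binary response, and the article defines no HbA1c threshold or responder category. As written, the plan yields no usable baseline-adjusted estimate of the primary effect. What is at stake is precision, and how far a chance difference in baseline HbA1c between the arms carries through to the result.

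The second is the reassurance about dropout. A participant with no 6-month HbA1c has no change score. Analysing people in the arm to which they were assigned does not alter that. If dropout is read to include loss to follow-up, the article offers intention to treat as a protection that it does not give.

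**Working it through.** **Inputs from the article.** Difference 0.5 HbA1c points, SD 1, two-sided alpha 5%, 90 participants per arm for power over 90%, 20% loss, total 216 (Sample size); 108 per arm (Study type). The article does not say whether SD 1 is the SD of change or of the HbA1c level.

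**Assumed.** The correlation r between baseline and 6-month HbA1c is not given, so r = 0.3 to 0.8 is used, with equal SDs at the two visits.

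**Step 1: the plan's own figure.** Power ≈ Φ(δ / (SD·√(2/n)) − 1.96). At n = 90: 0.5/√(2/90) = 3.354, and Φ(1.394) = 91.8% (91.6% with the noncentral t). The stated figure of over 90% is reproduced.

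**Step 2: participants with both measurements.** 108 × 0.8 = 86.4 per arm. At n = 86 power is 90.6% (90.3% with the noncentral t). About 216 × 0.2 = 43 participants would have no change score.

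**Step 3: change score against ANCOVA.** With a common SD s, Var(change) = 2s²(1 − r) and the ANCOVA residual variance is s²(1 − r²). The ratio is (1 − r²)/(2(1 − r)) = (1 + r)/2. Without equal SDs, the change-score variance exceeds the ANCOVA variance by (s_b − r·s_f)², where s_b and s_f are the baseline and follow-up SDs. This is never negative, so the direction does not depend on the equal-SD assumption, though the size does.

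If SD 1 is the SD of change:

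| Analysis | Variance ratio | Power at 86 per arm | n per arm for 90% power |
|---|---|---|---|
| t-test on change | 1 | 90.6% | 85 |
| ANCOVA, r = 0.3 | 0.65 | 98.2% | 55 |
| ANCOVA, r = 0.5 | 0.75 | 96.6% | 64 |
| ANCOVA, r = 0.7 | 0.85 | 94.5% | 72 |
| ANCOVA, r = 0.8 | 0.90 | 93.3% | 76 |

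If SD 1 is the SD of the level, the SD of change is √(2(1 − r)). Power at 86 per arm is then:

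| r | t-test on change | ANCOVA |
|---|---|---|
| 0.3 | 79.1% | 93.0% |
| 0.4 | 84.9% | 94.7% |
| 0.5 | 90.6% | 96.6% |
| 0.7 | 98.8% | 99.6% |

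On this reading the choice of test matters most at low correlation, where the t-test falls below the planned 90%.

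**Step 4: chance imbalance.** Given a baseline difference D between the arms, the change-score estimate moves by (1 − r)·D under equal SDs, which is half of D at r = 0.5. ANCOVA removes this. Over repeated randomisations D averages zero, so this is variance and not bias.

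**Step 5: what missing outcomes could do (illustration only).** Suppose the lost 20% of one arm had a change d smaller than that arm's completers, with no such gap in the other arm. The completer comparison is then off by 0.2·d: 0.10 for d = 0.5 (20% of the 0.5 target) and 0.20 for d = 1.0 (40%). Both values of d are assumed. Assignment as randomised leaves these amounts unchanged.

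**The case against.** The t-test is valid in a randomised trial, matches the stated outcome and the sample-size calculation, and keeps about 90% power at 86 per arm if SD 1 is the SD of change. On that reading the plan meets its own target. This stands: ANCOVA is an improvement in efficiency, not the repair of an invalid test. The size of the gain rests on a correlation that the article does not give.

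A reader might infer that the plan ignores baseline HbA1c. It does not: baseline is subtracted in the change score, and an adjusted analysis is planned. The fault is that the adjustment sits outside the primary analysis and in the wrong type of model. The logistic model might have been meant for a binary outcome such as non-adherence, for which a relative risk is planned, but the sentence ties it to the primary outcomes and adherence is listed as secondary.

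A reader might also infer that everyone without a 6-month value is dropped, so that this is a completer analysis called intention to treat. The article does not say so. A rule for missing data may stand in a full protocol or analysis plan that is not shown, and its absence from an article is not a fault.

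The dropout sentence has a milder reading. Paired with crossover, dropout may mean stopping the intervention, which analysis as randomised does address, and loss to follow-up is treated separately in the sample size. But the article draws no such distinction, so the sentence still reassures too much.

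Unequal retention between arms is possible, since better clinic attendance is hypothesised in the SMS arm. It is not shown: the inclusion criteria mention SMS reminders for the follow-up visit without limiting them to one arm.

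**Conclusion.** The point holds as one of precision and wording. The primary analysis leaves baseline HbA1c out as a covariate, and the planned adjusted model cannot be fitted to the continuous outcome as defined. Under equal SDs and assumed r of 0.3 to 0.8, ANCOVA removes 35% to 10% of the variance. If SD 1 is the SD of change, power at 86 per arm goes from about 90% to between 98% and 93%. If SD 1 is the SD of the level, the t-test has 79% to 85% power at r of 0.3 to 0.4, against 93% to 95% with ANCOVA.

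The documents do not support a claim that the t-test is biased or that participants are excluded. The intention-to-treat sentence is misleading only in so far as dropout covers the expected 20% loss to follow-up, and that calls for rewording.

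**What to change.** 1. Make the primary analysis a linear ANCOVA of 6-month HbA1c (or of the change) on arm, with baseline HbA1c, age and sex, which are the covariates already named. Let it replace the logistic model for this outcome, and keep the t-test as supportive. With baseline in the model, level and change give the same arm effect unless the change is rescaled for time between visits, so state which response is used.
2. Reword the intention-to-treat statement in Primary outcome measures and in Data analysis. It should say that participants stay in their assigned arm, which addresses crossover and stopping of the intervention, and that this does not by itself remove bias from missing 6-month HbA1c.
3. Report a sensitivity analysis for missing 6-month HbA1c beside the primary result. With no measurement between months 0 and 6, imputation from baseline data alone cannot correct losses that depend on the unseen outcome, so the sensitivity analysis should vary that assumption.

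The cost is analysis wording and modest programming. No extra participants, visits or measurements are needed.

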## Background

Diabetes mellitus, particularly type 2, is one of the most significant public health challenges of the 21^st^ century. More than 80% of diabetes related deaths occur in developing countries [1]. It is estimated that about 8.4 million people living in Bangladesh are suffering from diabetes already and by 2030, that number is expected to double, placing Bangladesh among the top five countries in terms of the absolute number of people living with diabetes [2]. Population data support an increasing trend in diabetes prevalence in Bangladesh, especially in urban areas where the prevalence is 8.1% compared to 2.3% in rural areas [3].

Non-adherence rates for therapies of chronic illness and for lifestyle changes are high with estimates ranging from 36% to 93% and averaging only 50% in developed countries [4,5]. Lack of adherence often leads to increased use of healthcare services, poor quality of life and increased healthcare costs [6,7]. In Bangladesh, adherence to medication is low due to several complex issues along with poor clinic attendance. This often leads to insufficient glycaemic control and avoidable life threatening complications. A recent study among newly diagnosed type 2 diabetes in Bangladesh reported 84% of patients had average to poor basic knowledge about their disease [8].

Mobile phone interventions for health are an emerging, rapidly-evolving practice and have been used to improve delivery of health services in many countries of the world [9]. Mobile phones can be a low cost solution to provide health education and increase adherence to treatment for people with chronic diseases like diabetes [10]. A study using mobile phone SMS by nurses in Korea found that SMS for 6 months reduced HbA1C in diabetic patients to 1.15% at 3 months and 1.05% at 6 months compared with baseline in the intervention group [11]. Mobile phone SMS have been shown to be an effective tool for providing diabetes health education, clinic and appointment reminders, medication reminders and for building awareness about the disease [12-14]. However, no data on the effects of such an approach on patient outcomes in resource-limited settings are available to date.

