### Hypothesis

Our primary hypothesis is that mobile phone SMS intervention is superior in reducing HbA1c in newly diagnosed type 2 diabetes compared to standard care. Secondary hypothesis is mobile phone SMS will increase diabetes knowledge, medication adherence and clinic attendance better in the interventions group than in the control group. The third hypothesis is participants in the mobile phone SMS group will have a better quality of life than participants in the control group. The fourth hypothesis is that mobile phone SMS will be a cost-effective measure for glycaemic control.

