### Secondary outcome measures

[Time Frame: 6 months]Diabetes knowledge (questionnaire)Self-reported medication adherence (Questionnaires)Clinic attendance (Clinic registers and questionnaires)Quality of Life (Self-reported questionnaires)Cost effectiveness of SMS interventions in reducing HbA1c

Description of outcome variables:Socio-demographic and economic information: Data on participant’s age, sex, religion, education, marital status, occupation, income, family size, family income, objects ownedMobile phone use and habits: Owns mobile phone, years of using mobile phone, can read SMS, can send SMS, frequency of sending SMS, monthly expenses for mobile phone and SMS, willingness to pay for SMS health advice/ medication reminder, maximum amount for mHealthKnowledge of prevention, management and complications of diabetes: Levels of knowledge and perceptions of diabetics, Risk Factors for diabetes, knowledge about prevention, management and complications of diabetes.Self-perceived Quality of Life Assessment: We will use EQ-5D tool and other modified tools to assess the Quality of Life for all participants. This questionnaire has been tested and validated to capture the difference in quality of life in chronic diseases patients.Self-reported diseases or disease prevalence: Self -reported information on different diseases and physical disability by the study participants.Medical History: Any known history of diabetics, CVD, hypertension, cancer, hypercholesterolemia, stroke, kidney diseases, other vascular disease, major surgery.Family history of diseases: Family history of diabetes, hypertension, heart diseases, stroke, kidney diseases, cancerMedication history: List of current and past medication taken by the patient, medication for diabetes, average monthly expenditure for medication, transportation to health facility/physician and consultation.Medication adherence: We will data on medication adherence of participants using different standardized tools and modifying to local context.Health seeking behaviour: Data will be collected on type of doctor visited during the past year, number of visits, distance travelled for consultation and expenditure for health.Tobacco Use (WHO modified questionnaire): A modified WHO questionnaire on use of different forms of tobacco currently and in the past with expenditure will be recorded.Physical Activity (GPAQ): WHO modified GPAQ questionnaire which has been validated in the fields will be used to capture information on different forms of physical activityDiet (WHO IMS/ Food Frequency Questionnaire): A modified and validated food frequency questionnaire will be administrated to ascertain food consumption pattern and dietary choices, type and frequency of consumption of different foods.Mental health status (PHQ9): The Patient Health Questionnaire PHQ 9 which is a standard tool for collecting mental health status in primary health care setting will be used.Life events and Disability: Life events related questions like new job, marriage, separation, injury, accident will be asked, which will be based on validated questionnaire.Anthropometric Measurements: Weight, Height, Mid-Upper Arm Circumference (MUAC), Waist and Hip circumference, Blood Pressure (BP), Pulse rate.Biological tests: Blood tests for HBA1C will be performed.

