## Abbreviations

SMS (Short Message Service): SMS is a way to send short messages using an alphabet, numbers, and symbols. SMS messages are digital information that can be transmitted over mobile networks, without Internet signal.
mHealt (Mobile Health): “the use of mobile computing and communication technologies in health care and public health” (Free et al. 2010 [9], p. 1).
Diabetes: Diabetes can be diagnosed on any of the following World Health Organization (WHO) criteria: Fasting plasma glucose (FPG) ≥7.0 mmol/l (126 mg/dl) or, 75 g oral glucose tolerance test (OGTT) with FPG ≥7.0 mmol/l (126 mg/dl) and/or 2 hour plasma glucose ≥11.1 mmol/l (200 mg/dl) or, Glycated haemoglobin (HbA1c) ≥6.5% / 48 mmol/l, or Random plasma glucose ≥11.1 mmol/l (200 mg/dl) in the presence of classical diabetes symptoms.
Asymptomatic individuals with a single abnormal test should have the test repeated to confirm the diagnosis unless the result is unequivocally elevated. Where a random plasma glucose level ≥5.6 mmol/l (≥100 mg/dl) and <11.1 mmol/l (<200 mg/dl) is detected: a FPG should be measured, or an OGTT performed, or an HbA1c measured.
Compliance: Has been defined as “the extent to which a person’s behavior coincides with medical advice”. Noncompliance then essentially means that patients disobey the advice of their health care providers. Patient noncompliance is attributed to personal qualities of the patients, such as forgetfulness, lack of will power or discipline, or low level of education.
Adherence: Adherence is defined as the “active, voluntary, and collaborative involvement of the patient in a mutually acceptable course of behavior to produce a therapeutic result.”
HbA1C: HbA1c indicates the level of diabetes control over the last 2-3 months and it is directly related to the occurrence of complicating events later in life

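### The only analysis stated for medication adherence is a yes/no relative risk; if the questionnaire gives a graded score, comparing the score would use the data better at almost no cost

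*Protocol article*

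**What the plan says.** The Research objectives section names medication adherence in its first objective, and the Hypothesis section includes it: "Secondary hypothesis is mobile phone SMS will increase diabetes knowledge, medication adherence and clinic attendance better in the interventions group". Under Secondary outcome measures, adherence is self-reported by questionnaire, and data are to be collected on "medication adherence of participants using different standardized tools and modifying to local context". The tool is not named, and its type of score is not described.

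The Data analysis section gives one statement specific to adherence: "Relative risk (RR) will be reported for non-adherence, with an RR less than 1 suggesting better outcome for the intervention group". A relative risk needs a yes/no outcome. The general rules at the end of that section assign the chi-square test and Fisher's exact test to categorical secondary outcomes, and logistic regression to quality of life and other continuous variables.

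**The concern.** Standardized adherence questionnaires may produce graded scores. If this one does, a split into adherent and non-adherent treats everyone on the same side of the cut as equal. Improvement that does not cross the cut is ignored, and the result depends on where the cut is placed. The general rules offer no way round this, because ordinary logistic regression also needs a binary outcome.

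The article gives adherence some weight. Its Discussion expects better knowledge to lead to better adherence and, through that, possibly to better glycaemic control. A weak adherence analysis would make it harder to see whether this step in the expected mechanism took place, whatever HbA1c shows.

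**Working it through.** **Inputs from the article**
- Two-sided 5% test: "an alpha error level of 5%, the two-tailed calculation gives a power of over 90% with only 90 participants in each arm of the study".
- Effect and SD for HbA1c: "Assuming that standard care with metformin reduces HbA1c by 1% on average and the intervention adds another 0,5" (percentage points), with "Assuming a SD of 1, which seems reasonable". The standardized effect is d = 0.5/1 = 0.5.
- 108 per arm. With the planned 20% loss, 216 × 0.8 / 2 = 86.4, so about 86 per arm.
- Background non-adherence in chronic illness: "estimates ranging from 36% to 93% and averaging only 50% in developed countries".

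**Assumptions, not in the article**
- The adherence score is roughly normal.
- The adherence effect is d = 0.2 to 0.5. The upper value is borrowed from HbA1c, because none is given for adherence.
- Control non-adherence p1 is 36% to 93%. This is the background range, not a design figure of this trial.

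**The article's own figure.** Power for a mean difference is Φ(d√(n/2) − 1.96). With n = 90 and d = 0.5 this is Φ(3.354 − 1.960) = 91.8%, which agrees with the stated figure of over 90%. With n = 86 it is Φ(3.279 − 1.960) = 90.6%. Both concern HbA1c; no power is stated for adherence.

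**Score against split, normal score.** Cut the same score so that a proportion p1 of controls is non-adherent. A shift of d gives p2 = Φ(Φ⁻¹(p1) − d) in the SMS arm. With p̄ = (p1 + p2)/2, the power of the two-proportion test is

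Φ{ [ |p1 − p2|√n − 1.96√(2p̄(1 − p̄)) ] / √(p1(1 − p1) + p2(1 − p2)) }.

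Example: n = 86, d = 0.5, p1 = 0.50. Then p2 = 0.309, the relative risk is 0.309/0.50 = 0.62, and power is Φ(0.416/0.681) = 72.9%, against 90.6% for the score.

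| n per arm | d | Score | Split, p1 = 36% | Split, p1 = 50% | Split, p1 = 93% | Loss (points) |
|---|---|---|---|---|---|---|
| 86 | 0.2 | 25.8% | 16.9% | 17.9% | 10.8% | 8 to 15 |
| 86 | 0.3 | 50.3% | 31.8% | 34.3% | 19.8% | 16 to 31 |
| 86 | 0.4 | 74.6% | 50.0% | 54.2% | 32.7% | 20 to 42 |
| 86 | 0.5 | 90.6% | 67.7% | 72.9% | 48.7% | 17 to 42 |
| 108 | 0.2 | 31.2% | 20.2% | 21.4% | 12.6% | 10 to 19 |
| 108 | 0.3 | 59.7% | 38.5% | 41.4% | 23.8% | 18 to 36 |
| 108 | 0.4 | 83.6% | 59.5% | 63.9% | 39.6% | 19 to 44 |
| 108 | 0.5 | 95.7% | 77.5% | 82.2% | 58.0% | 13 to 38 |

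The loss column also covers p1 = 64%, which sets the lower end in some rows. The largest losses all come from p1 = 93%. For 36% to 64% the loss is about 8 to 25 points.

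**Coarse score.** These are simulations with a latent normal shift and assumed category shares, comparing a rank test with the two-proportion test.
- Four levels, top level counts as adherent, 86 per arm. With 50% non-adherent: about 79% against 74% at d = 0.5, and 40% against 36% at d = 0.3. With 36% non-adherent: about 72% against 70%, and 35% against 32%. At 108 per arm the gaps are 2 to 6 points.
- Five levels with about half of controls non-adherent: a loss of about 3 to 12 points for d = 0.3 to 0.5.
- Five levels with only 10% non-adherent, which lies outside the background range: about 28 to 51 points.

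The split lost power in every case run, but the amount depends heavily on the tool and the cut.

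**The case against.** The article does not show that a graded score exists. It refers to standardized tools adapted locally, and the scoring may be set out in a fuller protocol or analysis plan that is not shown. Stating that a relative risk will be reported does not exclude a score analysis, and a relative risk of non-adherence is a legitimate, readable summary. A continuous adherence score would also fall under the rule for other continuous variables, so correcting that rule would cover much of the ground.

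Most of this stands, and it makes the point conditional. It does not remove it. The article makes a positive choice of a binary measure, and the rule for continuous variables names a method that again needs a binary outcome.

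Four stronger readings are tempting and are not supported:
- **A fixed loss of tens of points.** The effect, distribution and cut-off for adherence are all absent, and a coarse score can lose as little as 2 points.
- **Adherence as a key endpoint that the plan confines to a binary form.** It is one of several listed secondary outcomes, and the text does not limit its analysis to the relative risk.
- **The article itself defines adherence as a matter of degree.** The phrase "the extent to which a person’s behavior coincides with medical advice" belongs to its definition of compliance; adherence is defined separately and without such wording.
- **A published cut-off would fail after local adaptation.** The article does not say what will be adapted, so this cannot be judged.

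**Conclusion.** The point holds in conditional form. A relative risk of non-adherence is the only adherence-specific analysis stated, and no stated method would analyse a score on its own scale. If the tool is graded, the split costs power:
- about 8 to 44 points for a roughly normal score, under an assumed effect of 0.2 to 0.5 SD, control non-adherence of 36% to 93% and 86 to 108 per arm;
- about 2 to 6 points for a four-level score whose top category means adherent.

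If the tool is purely yes/no, there is no loss. The article makes no power claim for adherence, so none of its figures is wrong on this account, and the primary HbA1c comparison is unaffected. It is best treated as a cheap improvement.

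**What to change.** In the Data analysis section, state that where the adherence tool yields a graded score, the main adherence analysis is the between-arm comparison of the 6-month score, reported with a 95% confidence interval. Use ANCOVA with the baseline score as covariate where it was measured, or a rank or proportional-odds method if the score is coarse or skewed. Keep the relative risk of non-adherence as a supportive summary, at a cut fixed before unblinding.

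The cost is a sentence or two of wording, with no extra data, visits or participants. The downside is small: a score difference is harder to communicate than a relative risk, which is a reason to keep reporting both.
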